### Statistical analyses

To process and analyse the data we will use IBM SPSS Statistics [106], R [107], and MATLAB [108] software. Hypotheses will be tested using a significance level of *α* = .05. We will control type I errors in the primary analyses using Holm-Bonferroni corrections for multiple comparisons within each outcome analysis. No correction for multiple testing will be made in the exploratory analyses. We will report 95% bias-corrected and accelerated (BCa) bootstrap confidence intervals around all mean values.

Outliers are defined as scores outside ±3 SDs from the participant’s mean score for a task condition (participant-level data) or from the group mean (group-level data) for a particular test or task condition. We will examine participant-level and group-level RT data in the Hand Laterality Recognition and Directional Hypokinesia tasks for the presence of outliers and use nearest neighbour replacement if any are identified. We will use the same method of nearest neighbour replacement for the group-level outliers identified on the remaining outcome measures.

T-tests and ANOVAs will be conducted to compare mean values between groups and between data collection time points. Statistically significant interactions will be interrogated through follow-up contrasts. Wilcoxon signed-rank tests and Mann-Whitney U tests will be used if assumptions of t-tests are violated; however, ANOVAs are robust to moderate violations of normality and homogeneity of variance. Therefore, we will use ANOVAs unless severe violations of normality, homogeneity of variance, and sphericity assumptions are present, in which case we will use linear mixed models analyses with bootstrapping procedures.

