#### Primary outcomes

A change between RS2 (immediately before the commencement of treatment) and RS3 (immediately after the end of the treatment period) in current self-reported pain intensity and CRPS severity score [35, 52] are the primary outcomes. People with CRPS consider pain relief to be the highest priority for recovery [59], and pain intensity is the most common primary outcome in chronic pain trials [60]. Current pain intensity is measured using item 6 of the Brief Pain Inventory (BPI; short form) [42], which is a Numerical Rating Scale (NRS) ranging from 0 – “no pain” to 10 – “pain as bad as you can imagine”. The BPI has high reliability [42]. In addition to pain, CRPS involves a range of other debilitating symptoms, some of which were also affected by PA in previous studies [22, 24]. Therefore, we included a comprehensive measure of symptoms severity as the second primary outcome. The CRPS severity score assessment protocol follows the 16-points scoring system published by Harden and colleagues [35]. This continuous index of CRPS symptom severity has good discrimination abilities, concurrent validity and adequate sensitivity to change [35, 52], and has been recommended as one of the core outcome measures for CRPS clinical studies [61].

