#### Efficacy of PA treatment in reducing pain and CRPS symptom severity (RQ1)

A 2 × 6 ANOVA with Group as a between-subjects factor (PA treatment, sham treatment), and Time (RS1, RS2, RS3, RS4, LTFU1, LTFU2) as a within-subject factor will be conducted for the first primary outcome of pain intensity rating. We will also conduct sixteen a-priori contrasts to compare RS1 vs. RS2, RS2 vs. RS3, RS3 vs. RS4, RS2 vs. RS4, RS2 vs. LTFU1, RS4 vs. LTFU1, LTFU1 vs. LTFU2, and RS2 vs. LTFU2 within each group. We will also conduct a 2 × 4 ANOVA with the factors Group (PA treatment, sham treatment) and Time (RS1, RS2, RS3, RS4) for the second primary outcome of CPRS severity score, followed by eight a-priori contrasts comparing RS1 vs. RS2, RS2 vs. RS3, RS3 vs. RS4, and RS2 vs. RS4 within each group. We are primarily interested in detecting any changes between RS2 and RS3 which would represent immediate effects of treatment.

Minimisation factors (see Table 2) may be included as covariates in the ANOVAs if there are significant differences at RS1. Similarly, if we find significant group differences in the Profile of Mood States, Tampa Scale for Kinesiophobia, or Revised Life Orientation Test RS1 scores, these variables may be used as covariates in the ANOVAs on pain and CRPS severity score.

We will also calculate the Number Needed to Treat (NNT) separately for pain and CRPS severity score. The NNT will be based on the proportion of participants in each treatment arm that achieved clinically significant pain relief (≥2 points on 0–10 NRS scale [110]) and reduction in CRPS symptom severity (≥4.9 points [35]) in RS3 compared to RS2.

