While clearly defining our primary outcome measures, the trial includes a wide range of secondary outcome measures to assess the impact of treatment on pain and other clinical CRPS symptoms, as well as neuropsychological and emotional functioning, and symptoms’ interference with daily life. These measures will allow us to explore relationships between self-reported, clinical, and neuropsychological manifestations of CRPS from baseline data, independent of the primary research aim of testing the efficacy of PA.

Despite their informative value, large number of secondary outcomes might reduce the quality of data. To mitigate the potential impact of long duration and burden of research sessions, we composed a battery of assessments that would take no longer than 4 h to complete, including breaks between assessments. We also provide the participants with overnight accommodation near the research centre in cases when long travels are required, to minimise their fatigue during research sessions. In light of how little is known about cognitive changes in CRPS and effects of PA on these changes, broad battery of neuropsychological tests seems appropriate.

Furthermore, this research may identify potential individual differences accounting for the course of CRPS and response to treatment. The findings could provide an indication of how to identify the patients who are most likely to benefit from PA based on their cognitive and physical symptoms. This would inform subsequent research and therapies.

If PA brings benefits beyond that of the sham treatment on the primary outcome measures of the ongoing trial, this treatment should be developed as a recommended method to reduce pain and other CRPS symptoms. The study is likely to expand on our limited understanding of this debilitating condition and its neuropsychological components.

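### The two primary outcomes have no error control across them and no stated success rule; if either one counts as success, the chance of at least one false primary finding is about 8-10%

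*Protocol article*

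**What the plan says.** The Primary outcomes section states that changes between RS2 and RS3 in "current self-reported pain intensity and CRPS severity score [35, 52] are the primary outcomes". Severity has equal standing with pain: "Therefore, we included a comprehensive measure of symptoms severity as the second primary outcome".

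The Statistical analyses section sets the error level, "Hypotheses will be tested using a significance level of *α* = .05", and then the multiplicity rule, "We will control type I errors in the primary analyses using Holm-Bonferroni corrections for multiple comparisons within each outcome analysis". Exploratory analyses are left uncorrected.

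The RQ1 analysis section gives each outcome its own group-by-time ANOVA, its own contrasts and its own number needed to treat. For pain, "We will also conduct sixteen a-priori contrasts to compare RS1 vs. RS2" and seven further pairs of visits, in each group. For CRPS severity score there are eight contrasts: four pairs of visits in each group. The section adds: "We are primarily interested in detecting any changes between RS2 and RS3 which would represent immediate effects of treatment".

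The Discussion ties a recommendation to these results: "If PA brings benefits beyond that of the sham treatment on the primary outcome measures of the ongoing trial, this treatment should be developed".

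**The concern.** A trial with two primary outcomes has to say what counts as a positive result and how error is controlled over that decision. This protocol writes a multiplicity rule but draws its boundary around each outcome separately. The correction is spent on comparisons between visits within an arm, many of which (RS1 against RS2, or LTFU1 against LTFU2) are not the RS2-RS3 question. The two claims that matter for efficacy, prism adaptation against sham on pain and on severity, are not tied together by any rule.

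At stake is the reliability of a positive conclusion. With the success rule left open, a result significant on one outcome only could be presented as success or as failure after the data are seen, and the error rate attached to the recommendation is not known in advance.

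**Working it through.** **Inputs from the protocol.** Level 0.05 per hypothesis (Statistical analyses). Two primary outcomes (Primary outcomes). Contrast families of 16 and 8 (RQ1 analysis). Difference 2 points, SD 1.98, type I error 5%, power 90%, 21 per group (Sample size and power calculation). The protocol gives no correlation between the two outcomes, so a range is assumed.

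**1. The plan's own sample size.** Two-sided, normal approximation: n per group = 2 × 1.98² × (1.960 + 1.282)² / 2² = 20.6, rounded up to 21, or 42 in total. This reproduces the stated figure. Power at 21 per group is 90.5% by the normal approximation and 89.1% by the exact t-test. The calculation gives the full 5% to pain alone.

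**2. What the Holm families contain.** Pain: 8 pairs of visits × 2 groups = 16. Severity: 4 pairs × 2 groups = 8. Every member is a within-group time comparison. No between-arm contrast of RS2-RS3 change is listed for either outcome. The only between-arm test named is the group-by-time ANOVA, which spans all six (pain) or four (severity) visits.

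**3. Error if either outcome counts.** With each outcome tested at a two-sided 0.05:

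- Independent tests: 1 − 0.95² = 9.75%.
- Upper bound at any correlation: 0.05 + 0.05 = 10%.
- Correlated tests: 1 − P(|Z1| < 1.96 and |Z2| < 1.96), bivariate normal.

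| Assumed correlation of test statistics | At least one false finding | Both false |
|---|---|---|
| 0 | 9.75% | 0.25% |
| 0.3 | 9.5% | 0.5% |
| 0.5 | 9.1% | 0.9% |
| 0.7 | 8.3% | 1.7% |
| 0.9 | 7.0% | 3.0% |

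**4. The rule as written.** The 16- and 8-contrast Holm families were simulated with no true change, 21 per group, an assumed within-person correlation of 0.6, and 10,000 runs at each outcome correlation of 0, 0.3, 0.5 and 0.7. The chance of any rejection was about 4.5-4.7% within one outcome and 8.3-9.1% in at least one of the two. The rule does what it says within an outcome and nothing across them.

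**5. Error if both must be significant.** A false joint claim needs a false rejection on at least one outcome that is tested at 0.05, so its probability cannot exceed 5%. When neither outcome has an effect it is the last column of the table.

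**6. Cost of Holm across two tests.** The smaller p-value is compared with 0.025 and, if that succeeds, the other with 0.05. If the two tests are independent and each is held at 0.025, the chance of at least one false finding is 1 − 0.975² = 4.94%. Power for pain at 0.025 with 21 per group is 84.9% (normal) or 82.3% (exact t), against 90.5% or 89.1% at 0.05. Restoring 90% at 0.025 would need 2 × 1.98² × (2.241 + 1.282)² / 2² = 24.3, so 25 per group (26 by the exact t-test): 50 to 52 complete datasets instead of 42.

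**The case against.** The best defence is that the plan may intend both outcomes to succeed. The primary hypothesis joins pain and severity with 'and', and the Discussion speaks of benefit on the primary outcome measures in the plural. On that reading no correction across outcomes is needed. This stands as a possible reading, but neither sentence is a decision rule. Other features fit an either-outcome claim at least as well: the outcomes are analysed separately, each with its own number needed to treat, and the sample size rests on pain alone with no account of joint power.

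Independence is also the least plausible case, since the severity score itself includes pain, allodynia and hyperalgesia items. That is right, and it is why a range is given. At an assumed correlation of 0.9 the figure is 7.0%, still above 5%.

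Two stronger readings are tempting and should be resisted:

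- A reader might infer that the protocol claims a trial-wide 5% and misses it. It makes no such claim. It sets 0.05 per hypothesis and control within each outcome, and the 5% in the sample size section belongs to pain. The fault is an incomplete rule and not a false number.
- A reader might infer that Holm over 16 or 8 contrasts cuts the power of the primary between-arm test. The listed contrasts are all within-group and the between-arm RS2-RS3 comparison is not among them, so the documents show no such loss.

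**Conclusion.** The point holds. The multiplicity rule stops at the boundary of each outcome, and the plan states neither a success rule nor error control for the two primary claims together. If significance on either outcome counts as success, the chance of at least one false primary finding is about 8-10% for correlations from 0 to 0.7. If both are required, it does not exceed 5%. These figures assume two-sided tests at 0.05 for each outcome and no true effect on either; the correlations are assumptions, because the protocol gives none. Since the plan does not say which rule applies, the error rate behind its recommendation is undetermined.

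**What to change.** In Statistical analyses, define the confirmatory family as exactly two tests: the between-arm comparison of RS2-RS3 change in current pain, and the same comparison for CRPS severity score. Apply Holm across these two at an overall 0.05, and state that significance on either supports a claim for that outcome. Add both tests to the RQ1 analysis, where they are not now listed. Place the 16 and 8 within-group contrasts outside the family as secondary or descriptive.

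The cost is a short rewrite of two sections, to be made before unblinding, and some power: about 82% instead of 89% for pain at the first Holm step, with 21 per arm, a 2-point difference and SD 1.98.

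Two alternatives also hold 5% if stated in advance. A fixed order with pain first keeps pain at 0.05 and its 89% power, but severity can be claimed only if pain succeeds. An explicit both-required rule needs no lower alpha, but it reduces the power to meet the joint criterion, which the present sample size does not address.

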#### Sample size and power calculation

The required sample size was calculated based on the primary outcome measure of self-reported pain [109]. A meta-analysis defined a clinically significant reduction in pain as a change of Δ = − 2 (on a scale of 0–10) [110]. The sample size required to detect a pain reduction of this magnitude between RS2 and RS3 was estimated. The risk of type I error was set at 5% and the risk of type II error was set at 10%, giving 90% power to detect a significant change in the pain. The standard deviation expected in the current study was estimated as 1.98 based on pain intensity ratings obtained by our group in recent research [8]. Given these parameters, a minimum of 42 participants with CRPS (21 per group) is required to evaluate the effects of the PA treatment on the primary outcome measure of pain. Taking into account an anticipated drop-out rate of 20%, up to 52 participants with CRPS will be enrolled in order to obtain a total of at least 21 complete datasets for RS1-RS4 per treatment group. To provide normative data, 21 healthy (pain-free) control participants will be recruited.

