#### Treatment outcome analyses

We will conduct intention to treat (ITT) as our primary analysis to examine the overall effects of prism adaptation. The ITT analysis will include all allocated participants with CRPS regardless of treatment adherence and completion of outcome measurements. Baseline post-randomisation observation (RS2) carried forward will be used to account for missing data in ITT analysis, as the participants are expected to return to pre-treatment baseline over time. The exception is the Patient Global Impression of Change questionnaire that is only completed in the post-treatment research sessions, in which case the RS3 observation will be carried forward. Missing data from the computer-based tasks within each research session will be replaced by group mean for the particular task condition (with an exception of Directional Hypokinesia task, where some participant with CRPS may not be able to complete the task using the affected limb; in such cases only the conditions completed with the unaffected limb will be analysed). Missing daily logbook ratings will be interpolated using linear regression.

We will also conduct a supportive per-protocol (PP) analysis to see whether PA treatment can benefit the participants with CRPS who were able to perform it according to the trained protocol compared to those participants who were able to complete the sham treatment according to trained protocol [111]. The PP population will be the subset of the ITT population who provided complete outcome data for RS1-RS4 (i.e. attended all in-person research sessions and completed the primary outcome measures) and missed no more than 6 treatment sessions.

We will use confidence intervals to compare the RS1 primary outcomes scores of the participants with CRPS who withdrew and those who remained in the trial until RS4 to assess any potential selection bias. The timing and reasons for withdrawal will be presented in a CONSORT diagram.

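### The ±3 SD replacement rule reaches both primary outcomes without any check for error; separately, group-mean filling can understate variance on the secondary computer tasks

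*Protocol article*

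**What the plan says.** Statistical analyses defines a group-level outlier as a score more than 3 SD from the group mean for a test or task condition. Nearest-neighbour replacement is set first for reaction times in the Hand Laterality Recognition and Directional Hypokinesia tasks, and is then widened: "We will use the same method of nearest neighbour replacement for the group-level outliers identified on the remaining outcome measures". The two primary outcomes, the RS2-to-RS3 changes in current pain (0–10) and in the CRPS severity score (16 present/absent items), are not exempted. The rule asks for no sign that a value is wrong, and no analysis of unreplaced scores is mentioned.

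The RQ1 efficacy section derives an NNT from individual changes: at least 2 points for pain, and for severity a "reduction in CRPS symptom severity (≥4.9 points [35]) in RS3 compared to RS2". It does not say whether recorded or replaced scores are used.

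Treatment outcome analyses carries RS2 forward for missing outcomes, but treats the computer tasks differently: "Missing data from the computer-based tasks within each research session will be replaced by group mean for the particular task condition". Directional Hypokinesia conditions that cannot be done with the affected limb are excepted. Neither section says whether *group* means the treatment arm or all participants with CRPS.

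**The concern.** Replacing extreme reaction times is common, because very fast or very slow responses are often lapses. A self-rating of 0 on a pain scale, or a severity score of 5 out of 16, is not an artefact of that kind. It is the result for that participant. Replacing it alters a primary outcome by a rule that depends on how the other participants scored, and in the direction that matters most: the person who improved far more than the rest is moved back towards them. With 21 per arm, one reclassified responder changes a response proportion by 1/21, or 4.8 percentage points, and the NNT is built on those proportions.

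Mean filling is a different problem. A filled value adds to the count of observations but contributes no deviation of its own, so the SD and standard error of the filled data are too small. At stake are false-positive findings on the computer-task outcomes under RQ2.

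**Working it through.** **Planning SD.** The plan states: "The standard deviation expected in the current study was estimated as 1.98 based on pain intensity ratings". With a 2-point difference, two-sided 5% error and 90% power, the normal approximation gives n per arm = 2 × (1.960 + 1.282)² × 1.98² / 2² = 20.6, so 21. This reproduces the plan's figure ("a minimum of 42 participants with CRPS (21 per group) is required"). An SD of 1.98 and arms of 21 are used below.

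**When a lone value is flagged.** Let one value lie at distance d from the mean of the other 20, whose SD is s. Its distance from the overall mean is (20/21)d, and the overall variance is [19s² + (20/21)d²]/20. So

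z = (20/21)d / √{[19s² + (20/21)d²]/20}.

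- z exceeds 3 only if s/d < 0.237.
- If s = 1.98, d must be at least 1.98/0.237 ≈ 8.4 points on a 0–10 scale.
- If s = 0, z reaches its maximum of 20/√21 = 4.36, so the rule can fire.
- For two equal extreme values the maximum is 3.008, so in practice a pair protects itself.

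**How often, for pain.** Simulated normal scores with SD 1.98, rounded and held to 0–10, give any flagged value in 0.47%, 0.40%, 0.42% and 0.75% of arms at assumed means of 4, 5, 6 and 7. Truncating the distribution instead of piling scores at the ends gives about 0.3% at mean 5. The range is therefore about 0.3% to 0.8% per arm and time point.

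**What happens to a lone responder.** Assume one participant at 0 and the other 20 centred on 6.5.

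| SD of the others | Replaced in | Average shift of arm mean, against treatment |
|---|---|---|
| 1.0 | 99.8% of samples | 0.22 |
| 1.3 | 84% | 0.17 |
| 1.6 | 43% | 0.08 |
| 1.98 | 11% | 0.02 |

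With two or more such responders, nothing was ever flagged.

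**NNT illustration, severity score.** The documents give no SD for this score, so these values are invented: 5, 9, 10, five 11s, six 12s, five 13s, 14, 15. The mean is 245/21 = 11.67, the SD is √(82.67/20) = 2.03, and z for the 5 is −3.28, so it becomes 9. If that person scored 12 at RS2, a 7-point drop is analysed as a 3-point drop and misses the 4.9-point threshold. The case is near the edge: if the 9 were a 7, z would be −2.98 and nothing would change.

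**Mean filling, computer tasks only.** Suppose m of 21 whole scores per arm are filled with that arm's own observed mean, and let c = 21 − m. The difference between arms is unchanged. The SD is multiplied by √[(c − 1)/20], and the t statistic by f = √[(21/c) × 20/(c − 1)]. Type I error is 2·P(t on 2c − 2 df > 2.021/f).

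| m per arm (assumed) | SD factor | f | Type I error |
|---|---|---|---|
| 1 | 0.975 | 1.051 | 6.2% |
| 2 | 0.949 | 1.108 | 7.6% |
| 4 | 0.894 | 1.243 | 11.4% |

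By simulation, filling with the pooled CRPS mean leaves type I error at about 5%. Filling one of two averaged blocks (correlation 0.5 assumed) gives about 5.5%, 6.0% and 7.6%.

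**The case against.** The strongest reply concerns size and scope, and much of it stands.

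- **The replacement rule is nearly inert on the primary outcomes.** This is right for pain at the planning SD. Type I error is also barely affected: 4.9% with normal data and 5.8% with heavy-tailed data. A reader might infer that the rule routinely erases responders. The documents do not support that: it needs one isolated extreme, and replacement keeps the participant and moves the score to the nearest remaining one. A replaced pain responder may still pass the 2-point threshold.
- **Mean filling does not reach the primary outcomes.** Correct. Missing pain and severity scores take the RS2 value, so it would be wrong to say that filling shrinks their SDs.
- **The inflation depends on an unstated meaning of *group*.** Correct. The word is used elsewhere both for the treatment arms and for CRPS versus controls. Under the pooled reading the inflation disappears.
- **The missing rate is unknown.** Correct. The plan's drop-out allowance ("Taking into account an anticipated drop-out rate of 20%, up to 52 participants with CRPS will be enrolled") should not be read as the fill rate: the filling rule concerns gaps within a research session, and withdrawals are to be replaced by further recruitment.
- **The arithmetic is for one time point and whole scores.** Correct. The plan uses 2 × 4 ANOVAs, and filling is by task condition, while TOJ and Landmark average two blocks. The inflation is then smaller.

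None of this supplies a reason for replacing valid in-range primary scores, or a definition of *group*.

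**Conclusion.** The point holds in limited form. As worded, the outlier rule covers both primary outcomes and can alter a valid score. For pain the chance is small, about 0.3% to 0.8% of arms per time point if scores are roughly normal with SD 1.98. It rises only when one participant responds strongly and the rest of the arm is tightly clustered. The likely consequence is a smaller recorded benefit for that person and possibly a changed NNT status, if the NNT uses replaced scores. How often this would occur for the severity score cannot be judged from the document.

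Mean filling is a separate weakness, confined to the secondary computer tasks. Type I error of about 6%, 8% and 11% rests on three assumptions: own-arm means, whole scores filled, and 1, 2 or 4 missing per arm. It is smaller for partial filling and absent for pooled filling. Neither rule undermines the trial, but both are fixed choices that can only be neutral or harmful, and they should be corrected.

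**What to change.** 1. Restrict outlier replacement to reaction-time data, or to values shown to be recording errors.
2. State that valid pain, CRPS severity, questionnaire and clinical scores are analysed as recorded, and that the NNT uses recorded scores. Add a rank-based or robust analysis as sensitivity.
3. Define *group* wherever a group mean is used in data handling.
4. Drop group-mean filling. Analyse the observed task data with a linear mixed model, which Statistical analyses already names as a fallback, or use multiple imputation.

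The cost is analysis wording only, with no change to recruitment, visits or measurements. Intervals may be slightly wider. The change should be made before allocations are disclosed after the last RS4 visit.
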